### Statistical analyses

#### Primary outcomes

Differences in the change scores between the intervention group and the CAU group on the PCS of the RAND-36 will be analysed with linear mixed models according to the intention-to-treat principle as outlined in the Consolidated Standards of Interventional Trials (CONSORT) Statement with extension to cluster randomised trials [55]. This analysis technique allows for the clustering of patients within MHNPs and for dependence of observations within individuals over time.

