## Methods/design

This protocol was developed in accordance with the Standard Protocol Items: Recommendations for Interventional Trials (SPIRIT) Statement. For the SPIRIT Figure see Additional file 1 and for the SPIRIT Checklist see Additional file 2. We will conduct a parallel-group, multicentre, cluster randomised controlled trial in 39 primary care centres (a list of the participating centres is provided in Additional file 3). Cluster randomisation will take place at the MHNP and general practice level in order to avoid contamination between the intervention and control conditions. Clusters will be composed by matching MHNPs to all participating general practices where the MHNP works and to all other MHNPs who also work in these general practices. The entire cluster consisting of one or more MHNPs and general practices will then be randomly assigned to the intervention or to care as usual (CAU) group, prior to the inclusion of patients. An independent statistician, not involved in the selection of the practices and MHNPs, will carry out the randomisation. In order to balance the size of the intervention and CAU groups, randomisation will be stratified according to cluster size (small: less than 5000 patients, and large: 5000 patients or more). Assessments will take place at baseline (T0), during the intervention period at approximately 2 months (T1), directly after the intervention period at 4 months (T2), at 8 months (T3) and at 12 months (T4) after baseline.

This study is registered at the Dutch Trial Registry (NTR4686) and was approved by the VU Medical Center Ethics Committee. It will be conducted according to the principles of the Declaration of Helsinki (version 2013). Important protocol modifications will be communicated with the Dutch Trial Registry and the VU Medical Center Ethics Committee.

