### Power calculation/sample size calculation

We based the sample size calculation on an expected increase in the primary clinical outcome PCS of the RAND-36 during the total follow-up period (4 and 12 months after baseline). Based on previous findings, we aim to detect a clinically relevant effect size of 0.4. This effect size was previously shown to be feasible in a similar population [18]. The clinically relevant difference on the PCS ranges from 3 to 5 points [51]. Based on an estimate of the standard deviation of the PCS score of 10 [52], our effect size corresponds to a 4-point difference between the intervention group and the CAU group. We assume a two-sided significance level of 5% and a power of 80%. The ratio of the number of subjects in the compared groups is 1:1 and there are two measurements of follow-up for our primary outcome. Although we assume that the results will be similar on both repeated measurements, we opted for a more conservative correlation coefficient of 0.5. Using linear mixed models with these values leads to a sample size of *n* = 74 patients per condition.

However, since our study is a cluster randomised controlled trial, we applied an additional correction for the ‘design effect’ [53] with an expected average cluster size of four. As previous research found that 90% of intra-class correlation coefficients (ICCs) in primary care research are smaller than 0.055 [54], we chose an ICC of 0.05. After applying the correction, the sample size resulted in *n* = 85 patients (1.15 × 74) per condition. Taking a potential dropout rate of 20% into account, we aim to include 106 (85/0.8) patients in each condition.

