#### Secondary outcomes

Differences in change scores between the intervention group and the CAU group on the eight separate scales of RAND-36, HADS and PHQ-15 (secondary outcome measures) will also be analysed with linear mixed models according to the intention-to-treat principle.

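### The primary and secondary outcomes are compared as change scores; adjusting follow-up values for the T0 score would be more precise at no cost

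*Protocol article*

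**What the plan says.** Under Statistical analyses, Primary outcomes, the protocol article says that "Differences in the change scores between the intervention group and the CAU group on the PCS of the RAND-36" will be analysed by intention to treat with linear mixed models. It describes what the model handles: "This analysis technique allows for the clustering of patients within MHNPs and for dependence of observations within individuals over time". The Secondary outcomes paragraph repeats the approach: "Differences in change scores between the intervention group and the CAU group on the eight separate scales", together with the HADS and PHQ-15.

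Neither paragraph names a baseline covariate. The only sentence on adjustment, which concerns confounders and effect modifiers, stands in the Economic evaluation section. Table 2 shows that the PCS, the RAND-36 subscales, the HADS and the PHQ-15 are all collected at T0.

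Under Methods/design, "randomisation will be stratified according to cluster size". In the sample size section, "we aim to detect a clinically relevant effect size of 0.4"; with an SD of 10, "our effect size corresponds to a 4-point difference between the intervention group and the CAU group". The correlation of 0.5 given there refers to the two follow-up measurements (4 and 12 months). No correlation between baseline and follow-up is given.

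**The concern.** A change score subtracts the whole baseline value, so it fixes the coefficient on baseline at 1. With equal variances the best coefficient equals the baseline-to-follow-up correlation, which is below 1. Subtracting too much adds baseline noise to the comparison. It also lets regression to the mean move the estimate whenever the arms differ at baseline by chance.

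Three things are at stake:

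- Confidence intervals for the primary and secondary outcomes are wider than the collected data require.
- The planned power is exposed. The sample size rests on the SD of the PCS score itself and makes no use of baseline, so a change-score analysis matches it only if baseline correlates well enough with follow-up.
- The estimate depends on chance baseline differences. Whole clusters are randomised, with stratification by cluster size only, so such differences can arise.

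**Working it through.** **Inputs from the sample size section.** Difference 4 points, SD 10, two-sided 5%, power 80%, two follow-ups, follow-up correlation 0.5, ICC 0.05, average cluster size 4, dropout 20%.

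**Assumptions added here.** Variances are equal at all time points, and the same design effect applies to every analysis. The baseline-to-follow-up correlation r is not in the document; 0.5 is used for illustration and a range is shown.

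**Reproducing the plan.** One measurement per patient needs 2 × (1.960 + 0.842)² × 10² / 4² = 98.11 per condition. The mean of two follow-ups has variance factor (1 + 0.5)/2 = 0.75, and 98.11 × 0.75 = 73.6, so 74. The design effect is 1 + 3 × 0.05 = 1.15; 74 × 1.15 = 85.1, so 85; 85/0.8 = 106.25, stated as 106. The plan's figures reproduce as a comparison of follow-up means that ignores baseline.

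**Variance factors for the mean of two follow-ups** (units of SD², c = correlation between follow-ups):

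- baseline ignored: (1 + c)/2
- change score: (1 + c)/2 + 1 − 2r
- baseline-adjusted: (1 + c)/2 − r²

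**At c = r = 0.5.** Change score: 0.75 + 1 − 1 = 0.75. Baseline-adjusted: 0.75 − 0.25 = 0.50. The adjusted variance is 1 − 0.50/0.75 = 33% lower, and the change-score interval is √1.5 = 1.22 times as wide. The required n before clustering is 98.11 × 0.50 = 49.1, so 50, against 74. The planned effective size is 85/1.15 ≈ 74 per condition. There, adjusted power is Φ(0.4/√(2 × 0.50/74) − 1.96) = Φ(1.48) = 93%, against 80% for change scores.

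**One common correlation for all pairs:**

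| Correlation | Change score | Adjusted | Reduction |
|---|---|---|---|
| 0.3 | 1.05 | 0.56 | 47% |
| 0.5 | 0.75 | 0.50 | 33% |
| 0.7 | 0.45 | 0.36 | 20% |
| 0.8 | 0.30 | 0.26 | 13% |

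**Follow-up correlation held at the plan's 0.5, baseline correlation r varied:**

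| r | Change score | n, change score | Adjusted | n, adjusted |
|---|---|---|---|---|
| 0.3 | 1.15 | 113 | 0.66 | 65 |
| 0.4 | 0.95 | 94 | 0.59 | 58 |
| 0.5 | 0.75 | 74 | 0.50 | 50 |
| 0.6 | 0.55 | 54 | 0.39 | 39 |
| 0.7 | 0.35 | 35 | 0.26 | 26 |

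These n are per condition before the design effect and dropout. Below r = 0.5, change scores need more than the planned 74. At 74 effective patients their power is Φ(0.4/√(2 × 0.95/74) − 1.96) ≈ 70% at r = 0.4 and, with 1.15 in place of 0.95, about 62% at r = 0.3. The adjusted factor 0.75 − r² never exceeds the planning factor of 0.75.

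**Chance imbalance.** Given a baseline difference b between arms, the expected change-score estimate is the true effect plus (r − 1) × b. At r = 0.5 that is −0.5 points per point of imbalance. With the plan's figures, the standard error of the baseline difference is 10 × √(2 × 1.15/106) = 1.47. A difference of at least 2 points in either direction then has a chance of about 17%. It would move the estimate by 1 point, a quarter of the 4-point target.

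**Simulation.** 21 clusters of 4 per arm, ICC 0.05, all correlations 0.5, true effect 4, 4,000 runs. The mean estimate was 3.98 for both methods. The adjusted variance was 35% lower. Per point of baseline imbalance the change-score estimate shifted by −0.52 and the adjusted estimate by −0.02.

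**The case against.** The strongest reply is that the article names a model family and no covariates at all. A mixed model for change that also contains baseline as a covariate gives the same treatment effect as one for follow-up values with that covariate. The phrase might also be shorthand for a longitudinal group-by-time model. This stands as a caution: a full analysis plan may settle the matter. But the article does fix change scores as the quantity compared, for primary and secondary outcomes alike. A longitudinal model with unconstrained baseline means would not recover the lost precision. The stratum is a different matter: its absence from a condensed article is not an error in itself, and it is raised only as part of the same edit.

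Three stronger readings are tempting, and the document does not support them:

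- *The plan's own correlation implies a loss of a third.* The stated 0.5 links the two follow-ups, not baseline to follow-up. The authors also call it conservative, and with a higher common correlation the loss is smaller. No correlation is given for the secondary outcomes, so their loss cannot be sized.
- *Change scores make the result biased.* Under randomisation they are unbiased on average, as the simulation shows. The shift is conditional on an observed imbalance and is already part of the larger variance, so it should not be counted as a second defect.
- *Adjustment deals with recruitment after unblinded allocation.* If enrolment selects different patients in the two arms, baseline adjustment does not by itself remove that bias. This is a separate design question.

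**Conclusion.** The point holds as one of efficiency and robustness. The article fixes a change-score comparison and names no baseline covariate, although each outcome's T0 value is collected. With equal variances and 0.5 between all PCS measurements, baseline adjustment cuts the variance by 33% and raises power at the planned effective size from 80% to about 93%. Over common correlations from 0.3 to 0.8 the cut runs from about 47% to 13%.

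A reader might infer that the trial is underpowered because of this choice. At a baseline correlation of 0.5 it is not: the change-score variance equals the one behind the planned 74, and 80% is kept. Power falls short only if that correlation is below 0.5 with the follow-up correlation at 0.5. Type I error and the target of estimation are not affected. The change should be made because it gains precision and protects the planned power at no cost, not because the planned analysis is invalid.

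**What to change.** In the Primary outcomes paragraph of Statistical analyses, state that follow-up PCS values are modelled in the linear mixed model with T0 PCS as a covariate. A constrained longitudinal model with a common baseline mean is an equally good choice. Include the cluster-size stratum used in randomisation. In the Secondary outcomes paragraph, state the same for each RAND-36 subscale, the HADS and the PHQ-15, each with its own T0 value.

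The estimate remains the between-group difference in points, so the 4-point target keeps its meaning. The cost is a change of wording: no new measurements, patients or visits. It should be fixed, and dated, before outcome data are analysed; Trial status reports that recruitment was still under way at submission.

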#### Economic evaluation

*Cost-effectiveness analysis (CEA):* both a cost-effectiveness and cost-utility analysis will be performed from a societal perspective. The time period of the economic evaluation will be 12 months; therefore, discounting is not necessary. Sensitivity analyses will be performed to assess the robustness of the results using different assumptions regarding costs and effects.

Societal costs will be related to the following effect measures in the economic evaluation:Physical functioning as measured by the RAND-36Quality-adjusted life years (QALYs) based on the Dutch tariff for the EuroQol (EQ-5D-5L) [41]Severity of somatization (PHQ-15) and mental health (HADS)

The analysis will be done according to the intention-to-treat principle. Missing cost and effect data will be imputed using a multiple imputation technique. Incremental cost-effectiveness ratios (ICERs) will be calculated by dividing the difference in mean total costs between the groups, by the difference in mean effects between the groups. Bootstrapping with 5000 replications will be used to estimate 95% confidence intervals around cost differences and the uncertainty surrounding the ICERs. Rubin’s rules will be used to pool the results from the different multiply imputed datasets. Uncertainty surrounding the ICERs will be graphically presented on cost-effectiveness planes. Cost-effectiveness acceptability curves showing the probability that the intervention was cost-effective in comparison with usual care for a range of different ceiling ratios will also be estimated [56]. We will adjust for confounders and effect modifiers, when necessary*.*

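### Randomisation is stratified by cluster size, but the primary and secondary mixed models do not name that stratum; naming it as a fixed effect is a minor, almost free improvement

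*Protocol article*

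**What the plan says.** Under Methods/design, the protocol article describes the allocation: "In order to balance the size of the intervention and CAU groups, randomisation will be stratified according to cluster size". The two levels are "small: less than 5000 patients, and large: 5000 patients or more". This is the only restriction on randomisation that the article describes, and its stated purpose is balance in group size, not prognosis. The unit is the whole cluster: "The entire cluster consisting of one or more MHNPs and general practices will then be randomly assigned".

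Under Statistical analyses, Primary outcomes, change in PCS is compared between groups with linear mixed models by intention to treat, followed by: "This analysis technique allows for the clustering of patients within MHNPs and for dependence of observations within individuals over time". Under Secondary outcomes, the RAND-36 subscales, HADS and PHQ-15 "will also be analysed with linear mixed models according to the intention-to-treat principle". Neither paragraph mentions the stratum, and neither lists any fixed covariate.

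The one sentence on adjustment stands under Economic evaluation: "We will adjust for confounders and effect modifiers, when necessary". It does not name the stratum either.

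**The concern.** Stratified allocation balances small and large clusters across the arms, so a difference between the strata largely drops out of the treatment contrast. A model that omits the stratum still counts that difference as between-cluster error. If the stratum predicts PCS change, the reported standard error exceeds the true sampling error of the estimate, the interval is too wide, and the test rejects too rarely under the null. A random effect for MHNP, a different level for that random effect, or adjustment for baseline PCS does not bring the stratum into the model.

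What is at stake is some precision in a trial with few randomised units. There are 39 centres and a cluster may join several practices, so there are at most about 39 clusters. There is also a prespecification point: the Discussion says that researchers cannot be blinded to allocation, so adjustment choices are better fixed in advance.

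**Working it through.** **Inputs from the protocol article (Power calculation/sample size calculation):** difference 4 points, SD 10, two follow-ups with correlation 0.5, two-sided 5%, power 80%, average cluster size 4, ICC 0.05, dropout 20%.

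**The plan's own figure.**
- Variance of the mean of two follow-ups: 100 × (1 + 0.5)/2 = 75.
- n per arm = 2 × (10 × (1.960 + 0.842)/4)² × 0.75 = 98.11 × 0.75 = 73.6, so 74.
- Design effect 1 + (4 − 1) × 0.05 = 1.15; 74 × 1.15 = 85.1, so 85.
- 85/0.8 = 106.25, so 106 per arm and 212 in total.

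The figures reproduce. The calculation carries the full ICC and takes no credit for stratification.

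**Effect of leaving the stratum out.** Let f be the share of between-cluster variance that the stratum explains. The documents give no value, so f is an assumption, varied from 0 to 1. Also assumed: 85 analysed per arm, equal strata, and balanced allocation within strata.

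- Between-cluster variance: 0.05 × 75 = 3.75. Within-cluster variance: 71.25, or 71.25/4 = 17.8125 per cluster mean.
- Clusters per arm: 85/4 = 21.25.
- Variance reported without the stratum: 2 × (3.75 + 17.8125)/21.25 = 2.029, so SE = 1.425.
- True variance under stratified allocation: 2 × ((1 − f) × 3.75 + 17.8125)/21.25. At f = 0.25 this is 1.941 (SE 1.393); at f = 1 it is 1.676 (SE 1.295).
- SE ratio R = SE without stratum / true SE.
- Type I error without stratum = 2 × (1 − Φ(1.960 × R)).
- Power without stratum = Φ((4 − 1.960 × SE without)/true SE). Power with stratum = Φ(4/true SE − 1.960).
- PCS gap between strata implied by f: 2 × √(3.75 f).

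| f | Gap (points) | SE overstated | Type I error without | Power without | Power with |
|---|---|---|---|---|---|
| 0 | 0 | 0% | 5.0% | 80.2% | 80.2% |
| 0.10 | 1.22 | 0.9% | 4.8% | 80.4% | 80.9% |
| 0.25 | 1.94 | 2.3% | 4.5% | 80.7% | 81.9% |
| 0.50 | 2.74 | 4.7% | 4.0% | 81.3% | 83.6% |
| 1 | 3.87 | 10.0% | 3.1% | 82.5% | 87.1% |

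**Simulation check.** Cluster means were simulated for 44 clusters of four, with 40,000 runs per setting and a t-test. Without versus with the stratum:
- f = 0: power 79.6% vs 79.5%.
- f = 0.25: type I error 4.7% vs 5.1%; power 80.1% vs 81.4%.
- f = 1: type I error 3.1% vs 5.1%; power 81.6% vs 86.6%.

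**Sensitivity to layout.** With 39 centres, clusters may be fewer and larger. For clusters of five the cluster-mean variance is 3.75 + 71.25/5 = 18.0. At f = 0.25 the true value is 17.0625, R = √(18.0/17.0625) = 1.027, and the type I error is about 4.4%. The picture does not change.

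**Sensitivity to ICC.** At 0.10, the forgone gain is about 1.0, 2.4, 4.9 and 9.4 power points for f = 0.10, 0.25, 0.50 and 1. The protocol cites evidence that 90% of primary care ICCs lie below 0.055, so this is a pessimistic case.

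**The case against.** The strongest objection is that silence is not exclusion. The sentence on the mixed model describes two sources of correlation; it is not a list of model terms. No fixed covariate is named for any outcome, and a journal article commonly leaves that list to a full protocol or SAP, which are not shown here. This stands. A reader might infer that the authors chose to ignore the stratum, but nothing in the article says it will be left out.

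A reader might also infer that part of the planned power is lost. The figures do not support that. The sample size charges the full ICC, and power without the stratum does not fall below its f = 0 value at any share. Only a possible gain is forgone.

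Third, the effect depends on a link between cluster size and PCS change that the article never claims. It stratifies to balance group size. The larger rows of the table need strata that differ by 2.7 to 3.9 points, close to the 4-point target effect and to the 3 to 5 points the protocol calls clinically relevant. This also stands, and it makes the lower rows of the table unlikely.

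What remains after these concessions is that no text shown carries the design's one stratification factor into the analysis. The economic evaluation's sentence on adjusting when needed is not a prespecified rule for the clinical models.

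**Conclusion.** This is a minor point, worth a clarification. The stratum is used in the allocation and is not named in the primary or secondary models. If it is left out and if cluster size predicts PCS change, inference is conservative: the SE is too large by 0% to 10% and the type I error lies between 5.0% and about 3.1% at ICC 0.05. The forgone gain is 0 to about 1.2 power points for shares up to 25%, 2.3 at 50%, and 4.6 at the ceiling. False positives are not inflated.

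These sizes rest on the protocol's SD, correlation, ICC and cluster size, on equal strata with balanced allocation, and on an assumed stratum share for which the documents offer no evidence. If cluster size is unrelated to the outcome, nothing is lost.

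**What to change.** In Statistical analyses, Primary outcomes and Secondary outcomes, state that the randomisation stratum (fewer than 5000 versus 5000 or more patients, as used at randomisation) enters the linear mixed models as a prespecified fixed effect. Under Economic evaluation, name the same stratum within the adjustment already foreseen for costs and effects. If a full protocol or SAP already says this, a cross-reference is enough.

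The cost is a sentence of wording and one cluster-level degree of freedom. The stratum is known for every cluster before patients are included, so no new data are needed. If it turns out not to be prognostic, the loss is negligible: 79.6% versus 79.5% power in the simulation above.

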#### Secondary outcomes

Differences in change scores between the intervention group and the CAU group on the eight separate scales of RAND-36, HADS and PHQ-15 (secondary outcome measures) will also be analysed with linear mixed models according to the intention-to-treat principle.

#### Economic evaluation

*Cost-effectiveness analysis (CEA):* both a cost-effectiveness and cost-utility analysis will be performed from a societal perspective. The time period of the economic evaluation will be 12 months; therefore, discounting is not necessary. Sensitivity analyses will be performed to assess the robustness of the results using different assumptions regarding costs and effects.

Societal costs will be related to the following effect measures in the economic evaluation:Physical functioning as measured by the RAND-36Quality-adjusted life years (QALYs) based on the Dutch tariff for the EuroQol (EQ-5D-5L) [41]Severity of somatization (PHQ-15) and mental health (HADS)

The analysis will be done according to the intention-to-treat principle. Missing cost and effect data will be imputed using a multiple imputation technique. Incremental cost-effectiveness ratios (ICERs) will be calculated by dividing the difference in mean total costs between the groups, by the difference in mean effects between the groups. Bootstrapping with 5000 replications will be used to estimate 95% confidence intervals around cost differences and the uncertainty surrounding the ICERs. Rubin’s rules will be used to pool the results from the different multiply imputed datasets. Uncertainty surrounding the ICERs will be graphically presented on cost-effectiveness planes. Cost-effectiveness acceptability curves showing the probability that the intervention was cost-effective in comparison with usual care for a range of different ceiling ratios will also be estimated [56]. We will adjust for confounders and effect modifiers, when necessary*.*

*Budget impact analysis (BIA):* in the BIA, the cost-effectiveness of the short-term psychological intervention and usual care will be extrapolated using a simple Markov model over a period of 5 years based on the estimates obtained from the proposed study. Societal, government and insurer perspectives will be considered. Different scenarios will be evaluated including the following: (1) the intervention is not implemented, i.e. all patients receive usual care, (2) the intervention is offered to the whole patient population, (3) the intervention is implemented over a period of 4 years (25% of the patient population per year) and (4) the intervention is only offered to specific subgroups of the potential patient population. These subgroups will be defined based on the results of the study (e.g. subgroups that particularly benefitted from the intervention).

The total number of patients eligible for the intervention will be estimated based on Dutch incidence and prevalence rates of USD. Resource utilisation will be calculated by multiplying the number of eligible patients with the resource utilisation rates obtained from the cost-effectiveness analysis. Different prices will be used to value resource use depending on the perspective of the analysis: Dutch standard costs for the societal perspective, actual Dutch Healthcare Authority (NZA) tariffs for the government perspective, and average NZA tariffs for the insurer perspective. Both resource use and annual costs will be presented over a 5-year period for all perspectives. Aggregated and disaggregated (e.g. GP care, secondary care, and productivity losses) total costs per year will be presented for the different perspectives and scenarios.

*Analysis of patients most likely to benefit from the intervention*: if power allows, interaction terms between potential effect modifiers (e.g. severity, comorbidity, gender) and group allocation will be tested in mixed regression models. In case of insufficient power, only exploratory analyses will be done.

*Mediation analyses*: mediation analyses will be conducted to determine whether the intervention affected physical functioning through changes in problem-solving skills, health anxiety, illness perceptions, coping, mastery and/or working alliance. The Krull and MacKinnon method [57] will be used for this purpose.

*Factors influencing implementation*: data will be obtained on participation rate, satisfaction with the intervention and characteristics of non-responders. Data collected from non-responders will be limited to demographic characteristics, such as age and gender and reasons for not participating in the study. Impeding and facilitating factors for implementation as observed by MHNPs will be ascertained by conducting interviews with the latter. The interviews will be transcribed verbatim. The transcripts will be analysed by coding the texts using Atlas.ti and themes will be identified and described.

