#### Primary outcomes

The primary clinical outcome of this study is the improvement in physical functioning during the total follow-up period measured by the physical component summary score (PCS) of the RAND-36-item Health Survey (RAND-36). The RAND-36 is a widely used, valid and reliable health-related quality of life (HRQoL) instrument comprising 36 items that assess eight health domains: physical functioning, role limitations caused by physical health problems, role limitations caused by emotional problems, social functioning, emotional wellbeing, energy/fatigue, pain and general health perceptions [37–39]. Physical and mental health summary scores (PCS and MCS, respectively) can be derived from the eight scales. The raw scores are transformed into scores ranging from 0 to 100 with a higher score indicating better functioning.

The primary outcome for the economic evaluation is quality of life as measured by the EuroQol 5D – 5 level version (EQ-5D-5L) [40]. The EQ-5D-5L is a standardised instrument including five health domains (mobility, self-care, usual activities, pain/discomfort and anxiety/depression). It comprises five items, one single item referring to each domain, that are assessed on a 5-point scale: 0 = ‘no problems with’, 1 = ‘slight problems with’, 2 = ‘moderate problems with’, 3 = ‘severe problems with’ and 4 = ‘unable to’. The health state indicated by patients on the EQ-5D-5L will be converted to a utility score using the Dutch EQ-5D-5L tariff [41]. The EQ-5D-5L utility scores at different time points will be used to calculate quality-adjusted life years (QALYs) using the area under the curve method. Changes between health states at different time points are considered to be linear. Also, the patient is asked to rate their general health on a 0–100 scale [40].

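### The economic evaluation makes no stated provision for the randomised clusters and leaves baseline adjustment to an undefined 'when necessary'

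*Protocol article*

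**What the plan says.** The trial is cluster randomised. Methods/design states "We will conduct a parallel-group, multicentre, cluster randomised controlled trial in 39 primary care centres", and on allocation: "The entire cluster consisting of one or more MHNPs and general practices will then be randomly assigned". This happens before patients are included. The sample size section applies a design effect for an average cluster size of four and an ICC of 0.05. Under Statistical analyses, the linear mixed model for the PCS compares change scores and is said to account for patients being clustered within mental health nurse practitioners (MHNPs). The secondary outcomes also use linear mixed models.

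The Economic evaluation section is fairly detailed. Missing costs and effects are multiply imputed and pooled by Rubin's rules. ICERs are obtained "by dividing the difference in mean total costs between the groups, by the difference in mean effects between the groups". On uncertainty it says "Bootstrapping with 5000 replications will be used to estimate 95% confidence intervals around cost differences and the uncertainty surrounding the ICERs", with cost-effectiveness planes and acceptability curves to follow. Clusters are not mentioned for the estimator, the bootstrap or the imputation. On covariates it says only "We will adjust for confounders and effect modifiers, when necessary".

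Under Outcome measures, the EQ-5D-5L "utility scores at different time points will be used to calculate quality-adjusted life years (QALYs) using the area under the curve method", with linear change between time points. Table 2 places the EQ-5D-5L at 0, 2, 4, 8 and 12 months and the Tic-P cost questionnaire at 0, 4, 8 and 12 months.

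**The concern.** Two separate gaps meet in one analysis.

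- **Clustering.** Patients in the same cluster share practices and nurses, so their costs and utilities may be correlated. A bootstrap that draws patients one at a time treats them as independent, and an imputation model without cluster can weaken the correlation further. The intervals, the planes and the acceptability curves would then look more certain than the design allows.
- **Baseline.** A QALY computed as an area under the curve contains the baseline utility itself, as well as later utilities that correlate with it. The PCS analysis at least works on change scores, whereas the QALY analysis commits to no handling of baseline. A rule that adjusts when this seems necessary lets the observed data decide the estimator.

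Baseline imbalance is plausible here. There are few units of allocation, patients are screened and consent after their cluster has been allocated, and the Discussion states that patients, providers and researchers cannot be blinded. Cost-effectiveness is one of the two stated aims, and the five-year budget impact model is built on the trial's estimates.

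**Working it through.** **1. The plan's own figures.** Inputs from the sample size section: difference 4, SD 10, two-sided 5%, power 80%, two follow-up measurements with correlation 0.5, cluster size m = 4, ICC 0.05, dropout 20%.

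- Per arm for one measurement: 2 × [10 × (1.960 + 0.842) / 4]² = 98.1
- Two measurements: 98.1 × (1 + 0.5)/2 = 73.6, so 74
- Design effect: 1 + (4 − 1) × 0.05 = 1.15, and 74 × 1.15 = 85.1, so 85
- Dropout: 85/0.8 = 106.25, stated as 106, which gives 212 in total

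The stated 74, 85 and 106 are reproduced.

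**2. What patient-level resampling would cost.** This step applies only if patients are resampled singly. With design effect DE = 1 + (m − 1) × ICC, the ratio of naive to correct interval width is 1/√DE, and the actual coverage of a nominal 95% interval is 2Φ(1.96/√DE) − 1.

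The plan gives no ICC for costs or QALYs. The 0.05 was chosen for the PCS, and the other values are assumptions. The second cluster size assumes that the 39 centres are the randomised clusters: 212/39 = 5.44. All 212 are counted because the analysis is by intention to treat with imputation.

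| m | ICC | DE | Width ratio | Coverage |
|---|---|---|---|---|
| 4 | 0.01 | 1.03 | 0.985 | 94.7% |
| 4 | 0.02 | 1.06 | 0.971 | 94.3% |
| 4 | 0.05 | 1.15 | 0.933 | 93.2% |
| 4 | 0.10 | 1.30 | 0.877 | 91.4% |
| 5.44 | 0.05 | 1.222 | 0.905 | 92.4% |
| 5.44 | 0.10 | 1.444 | 0.832 | 89.7% |

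These are normal-theory results. A small simulation with skewed costs (27 clusters of 4 per arm, 1000 runs) did not clearly separate the two schemes. Patient-level against cluster-level coverage was 94.0% against 94.8% at ICC 0.05, and 90.9% against 91.4% at ICC 0.10. With 1000 runs the standard error of a coverage near 95% is √(0.95 × 0.05/1000) = 0.7 percentage points, so differences of this size cannot be resolved. The simulation is not relied on here.

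**3. How baseline utility enters the QALY.** With measurements at 0, 2, 4, 8 and 12 months, the trapezoid rule gives weights of 1/12, 2/12, 3/12, 4/12 and 2/12 of a year, which sum to 1. Suppose a baseline difference carries over to each later time point in proportion to a common correlation r (an assumption, with equal variance over time). The share that reaches the unadjusted QALY difference is 1/12 + r × 11/12.

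| r (assumed) | Share | QALY from an assumed imbalance of 0.03 |
|---|---|---|
| 0.3 | 0.358 | 0.011 |
| 0.5 | 0.542 | 0.016 |
| 0.7 | 0.725 | 0.022 |

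**The case against.** The strongest objection is that much of this is inferred from silence. A reader might conclude that the plan uses an unclustered bootstrap and that its intervals are therefore too narrow. The article does not say so: the resampling unit and the imputation model are simply not stated, and a condensed article may leave them to a fuller document. This stands, so every coverage figure above is conditional on patient-level resampling and a positive ICC.

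The adjustment clause also does not exclude baseline utility, which would be an obvious candidate if it were imbalanced. Dividing one mean difference by another defines an ICER and does not commit the plan to unadjusted means. So it cannot be said that imbalance will pass into the QALY result, nor that imbalance could set the direction of the cost-effectiveness conclusion: the article gives no expected QALY effect and no utility SD to judge that by.

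A reader might also infer that listing effect modifiers as adjustment variables biases the comparison. It does not. The candidates under Patient and illness characteristics are baseline variables that may be prognostic, and including them as covariates is legitimate. The wording is loose, since effect modification is a question for the interaction terms planned separately.

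Finally, 0.05 is a high-end ICC by the plan's own account, and at 0.01 to 0.02 the loss of coverage is under one percentage point.

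What the objection does not remove is the adjustment rule. It is stated rather than omitted, it depends on the data, and it gives neither covariate nor criterion. Nor does it explain why clustering is explicit for the sample size and the PCS but absent from an otherwise specific description of the economic analysis.

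**Conclusion.** The point holds as a conditional one. The economic evaluation states its estimator, imputation and bootstrap without any provision for the randomised clusters, unlike the PCS analysis, and replaces a prespecified baseline adjustment with an open rule.

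- If patients were resampled singly, the plan's own m = 4 and ICC 0.05 imply intervals about 7% too narrow and 93.2% coverage. With the 39 centres as clusters (assumed), the figures are 9.5% and 92.4%. At an assumed ICC of 0.10, coverage is 91.4% and 89.7% respectively. This is a modest loss.
- If QALYs were left unadjusted, about 36% to 73% of any baseline utility difference would enter the QALY difference, for assumed correlations of 0.3 to 0.7. An assumed imbalance of 0.03 gives 0.011 to 0.022 QALY.

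The PCS analysis is not affected. The case for changing the text is that a better rule is nearly free and bears on the intervals and acceptability curves for one of the trial's two aims.

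**What to change.** In the Economic evaluation section:

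- State that the bootstrap resamples whole randomised clusters within arm. A two-stage cluster bootstrap, or a bivariate multilevel model for costs and effects, would also serve.
- State that the imputation model includes the randomised cluster.
- Replace the 'when necessary' sentence with a fixed rule: QALYs adjusted for baseline EQ-5D-5L utility, costs for baseline Tic-P costs, and the RAND-36 physical functioning, PHQ-15 and HADS effects each for their own baseline value. Leave effect modification to the interaction analyses already planned.

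The cost is wording, some extra programming and slightly wider intervals. Table 2 shows that every baseline measure needed is already collected.
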